### 2.2. Study Participants

The inclusion criteria will be:Person who currently smokes ≥5 cigarettes per day [25] (conventional cigarette or equivalent in nicotine content from HTP or ENDS);Adult persons who smoke (≥18 years old);Ability and willingness to provide informed consent or presence of a legal representative who consents.

The exclusion criteria will be:Persons < 18 years old;Pregnant or breastfeeding women;Current or past use of pharmacological or behavioral smoking cessation supports [25];Concurrent dependence on alcohol or other substances of abuse (excluding nicotine) [25];Advanced neurocognitive degenerative disorders;Unstable psychiatric conditions (including active suicidal ideation, recent psychiatric hospitalization, and/or changes in psychiatric medication within the past 3 months) [26,27];Inability or refusal to provide informed consent;Inability to access the integrated telemedicine platform and/or use wearable remote-monitoring devices;Participants without access to home medical devices for monitoring cardiopulmonary parameters (blood pressure monitor and pulse oximeter), required to perform the scheduled home assessments.

No restrictions regarding gender, race, nicotine addiction, or motivation to quit smoking will be enforced.

### 2.3. Remote Smoking Cessation Program Assisted by Wearable Monitoring Devices (Experimental Protocol)

A tailored, multimodal behavioral smoking cessation telerehabilitation program assisted by non-invasive wearable remote-monitoring devices will be used for the EG. The program will be integrated with wearable devices and the web-based telemedicine platform BTS TELEREHAB: https://www.btsbioengineering.com/it/products/bts-telerehab/ accessed on 26 May 2026 (BTS Bioengineering S.p.A., Garbagnate Milanese, Italy), accessible via dedicated workstations and/or mobile devices operating on Android or iOS systems.

Participants will receive individualized behavioral and psychological support in accordance with the national clinical guidelines to promote smoking cessation by the Italian Ministry of Health and the National Institute of Public Health (freely available on https://www.salute.gov.it/imgs/C_17_pubblicazioni_832_allegato.pdf, accessed on 12 May 2026), including individual counseling, cognitive behavioral therapy, and motivational interventions aimed at promoting smoking cessation, increasing awareness of the harmful effects of tobacco and nicotine-containing products, identifying smoking triggers, and preventing relapse throughout the rehabilitation process.

All behavioral counseling and support components are standardized between the experimental arm and the control arm; only the delivery modality differs.

The intervention includes periodic counseling sessions focused on smoking cessation, lifestyle modification, pharmacological adherence, and psychological support. These sessions are scheduled at the time of the routine outpatient follow-up visits, which occur with the same frequency in both study arms according to standard clinical practice. The duration of each session is approximately 30 min.

Specialist-specific contributions are as follows:Cardiologists: optimization of cardiovascular risk factors, therapeutic management, motivational support for smoking cessation, and counseling on the cardiovascular benefits of quitting smoking.Respirologists: assessment and management of respiratory comorbidities, pulmonary function evaluation, support for smoking-related respiratory issues, and counseling on the respiratory benefits of quitting smoking.Dentists: evaluation of oral health, management of smoking-related periodontal disease, and counseling on the oral benefits of quitting smoking.Psychologists: structured behavioral counseling, motivational interviewing techniques, management of psychological dependence, and emotional support.

All sessions are documented in the electronic health record to ensure traceability, reproducibility, and consistency between the two study arms.

On a voluntary basis, participants allocated to the study group will be asked to use the wearable remote-monitoring devices and record physiological parameters twice a day, for a maximum duration of the study of 12 months.

Following enrollment, the EG will receive training on the use of the integrated telemedicine platform and the wearable monitoring devices after the calibration of the devices.

The wearable devices will record participants’ cardiopulmonary parameters (heart rate, blood pressure, respiratory rate, and oxygen saturation) on the integrated telemedicine platform. In this way, the participant’s medical parameters will be automatically recorded through the wearable device and automatically transferred to the telemedicine platform.

Participants will also complete a paper-based smoker diary developed by the Italian Ministry of Health and the National Institute of Public Health (freely available on https://smettodifumare.iss.it/documents/d/guest/guida-smetto-di-fumare-a5-v07, accessed on 12 May 2026), recording the daily number and frequency of cigarettes or nicotine-containing products used.

Adherence to wearable device utilization will be automatically tracked through the telemedicine platform by recording the timing and frequency of device use.

Participants in the EG will also self-report oral health-related parameters, including gingival bleeding during daily oral hygiene procedures performed at least twice a day throughout the rehabilitation program.

All detected smoking events and recorded parameters will be automatically transmitted to the telemedicine platform. In this way, the smoker’s diary will be automatically compiled through the wearable device recordings.

Finally, the integrated telemedicine platform and remote wearable monitoring devices will send push notifications to remind patients to take prescribed medications (particularly for fragile patients and those with comorbidities) at scheduled times.

The telemedicine platform and wearable devices will also periodically send text messages, photos, and videos to support smoking cessation.

Healthcare providers involved in the multidisciplinary smoking cessation program, including dental, cardiologic, pneumological, and psychological specialists, will be able to remotely monitor participants throughout the telerehabilitation program. When clinically necessary, treatment modifications may be proposed and shared among specialists and participants.

At any time, the patient will be able to request and schedule teleconsultation sessions via videoconference with the selected healthcare specialist through the integrated telemedicine platform, and vice versa. An in-person clinical evaluation should be scheduled if deemed necessary by the clinician.

The integrated telemedicine platform and wearable monitoring system will comply with applicable data privacy and security regulations.

Both the integrated telemedicine platform and wearable remote-monitoring devices will ensure compliance with data privacy and protection standards.

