#### 2.3.2. Wearable Remote-Monitoring Devices

The wearable remote-monitoring devices integrated with the BTS TELEREHAB platform are medical-grade, non-invasive tools, including wireless inertial sensors (e.g., G-SENSOR) and pulse oximeters (BTS Bioengineering S.p.A., Garbagnate Milanese, Italy). They collect the following physiological parameters: heart rate, blood pressure, respiratory rate, and peripheral oxygen saturation. Measurements will be collected twice daily for up to 12 months.

Data are acquired by the wearable devices and transmitted in real-time via a secure Bluetooth connection to the patient’s mini-PC Brain unit, which then forwards them to the cloud-based BTS TELEREHAB platform (https://www.btsbioengineering.com/it/products/bts-telerehab/ accessed on 26 May 2026) through an Internet connection (provided there is access to Wi-Fi or a portable hotspot). Data transmission uses encrypted protocols compliant with GDPR.

The system is designed for home and clinical use and has been validated in rehabilitation and telemedicine settings, as described in the BTS TELEREHAB (BTS Bioengineering S.p.A., Garbagnate Milanese, Italy) manuals.

Adherence to device use and data quality will be automatically monitored by the platform.

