### 2.4. Standard Smoking Cessation Program (Control Protocol)

A tailored, multimodal behavioral smoking cessation rehabilitation program delivered exclusively through in-person care will be used for the CG. The behavioral and psychological interventions provided to the CG will be equivalent to those delivered to the EG (described in Section 2.3), differing only in the mode of delivery, namely, face-to-face assistance rather than telemedicine-based rehabilitation.

The behavioral and psychological interventions will be provided during follow-up visits in order to address behavioral difficulties, maintain motivation, and support long-term abstinence.

For home monitoring of cardiopulmonary parameters, portable medical devices already available in participants’ possession, such as sphygmomanometers and pulse oximeters, will be used to manually record heart rate, blood pressure, respiratory rate, and oxygen saturation twice a day for up to 12 months. Unlike the EG, physiological parameters in the CG will not be automatically transmitted to a telemedicine platform, and no wearable remote-monitoring devices will be used. No participant will be required to independently purchase portable medical devices in order to participate in the study, according to the aforementioned exclusion criteria for the CG.

Similar to the EG, participants allocated to the CG will complete a paper-based smoker diary developed by the Italian Ministry of Health and the National Institute of Public Health (freely available on https://smettodifumare.iss.it/documents/d/guest/guida-smetto-di-fumare-a5-v07, accessed on 12 May 2026), recording the daily number and frequency of cigarettes or nicotine-containing products used.

Participants in the CG will also self-report oral health-related parameters, including gingival bleeding during daily oral hygiene procedures performed at least twice a day throughout the rehabilitation program.

Healthcare providers involved in the multidisciplinary smoking cessation program, including dental, cardiologic, pneumological, and psychological specialists, will monitor participants exclusively through scheduled in-person visits according to the rehabilitation program and participants’ clinical needs. Additional in-person specialist evaluations may be scheduled whenever considered clinically necessary.

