### 2.5. Outcomes and Data Collection

#### 2.5.1. Primary Outcome

The primary outcome of the study will be the effectiveness of the program on smoking cessation, assessed through Continuous Abstinence Rates (CARs) and Point Prevalence Abstinence (PPA).

CARs will be defined as sustained smoking abstinence throughout the follow-up period without relapse [28]. CARs will be calculated as the proportion of participants who maintain continuous smoking abstinence at the 6-month and 12-month follow-up assessments without relapse during the observation period.

PPA will be defined as abstinence from smoking at the time of assessment, regardless of any previous smoking relapses during follow-up [28]. PPA will be calculated as the proportion of participants reporting abstinence from smoking at the 6-month and 12-month follow-up assessments, regardless of previous smoking relapses during follow-up.

Both CARs and PPA will be assessed using self-reported smoking status collected through the smoker diary and will be computed 6 and 12 months after baseline [28]. Smoking abstinence outcomes will be assessed through self-reported smoking status, consistent with the telemedicine-based design of the Wear-Smile project.

No biochemical verification of smoking abstinence (e.g., exhaled carbon monoxide or cotinine testing) will be performed.

The timing at 6 and 12 months to assess smoking behavior status was established because a 6-month abstinence period was considered indicative of long-term smoking cessation, as it allows for a more reliable estimation of the proportion of participants who will maintain abstinence even in the subsequent years [8]. A permanent effect of smoking cessation treatment was estimated to be 50% of the Continuous Abstinence Rate at 6 months [8].

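### The protocol gives two incompatible accounts of how the experimental arm's smoker diary is filled in, and that diary is the named source of both primary outcomes

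*Protocol article*

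**What the plan says.** **Source of the primary outcome.** Section 2.5.1: "Both CARs and PPA will be assessed using self-reported smoking status collected through the smoker diary". The same section rules out carbon monoxide and cotinine testing.

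**Experimental arm, first account.** Section 2.3: "Participants will also complete a paper-based smoker diary", in which the daily number and frequency of products used are entered.

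**Experimental arm, second account.** Later in Section 2.3: "All detected smoking events and recorded parameters will be automatically transmitted to the telemedicine platform". The next sentence adds that the "diary will be automatically compiled through the wearable device recordings".

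**Control arm.** Section 2.4: "Similar to the EG, participants allocated to the CG will complete a paper-based smoker diary". The same section states that this arm uses no wearables.

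**Secondary outcome.** Section 2.5.2 records daily consumption in the paper diary and makes no distinction by arm.

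**Devices.** Section 2.3.2, on what the wearables record: "They collect the following physiological parameters: heart rate, blood pressure, respiratory rate, and peripheral oxygen saturation". Readings are twice daily, and Section 2.3 makes use of the devices voluntary.

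**The concern.** A diary that the participant fills in on paper and a diary that a device fills in are different instruments with different errors. The automatic route can exist in one arm only. If it were used, CAR and PPA would be device-derived in the experimental arm and self-reported in the control arm. Misclassification would then depend on allocation, and neither randomisation nor an intention-to-treat analysis removes that. The trial is also unblinded, and no biochemical check could show the error or correct it.

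The automatic route has two further weaknesses. No described measurement would supply the smoking events. And because device use is voluntary and readings are taken twice a day, a gap in device use could leave an empty diary that reads as abstinence.

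**Working it through.** **1. The statements side by side**

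| Place | Arm | Diary |
|---|---|---|
| 2.3, diary paragraph | Experimental | Paper, completed by the participant |
| 2.3, smoking-events paragraph | Experimental | Compiled automatically from the wearable |
| 2.4 | Control | Paper, completed by the participant, said to be like the experimental arm |
| 2.5.1 | Both | Self-report through the diary |
| 2.5.2 | Both | Paper |

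The second row conflicts with all the others. It also conflicts with the device descriptions in Sections 2.3 and 2.3.2, which list four cardiopulmonary parameters and no smoking event.

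**2. Inputs for an illustration**

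- Group size: 51 per arm (Section 2.6). This reproduces as a one-sided t-test with α = 0.05, power 0.80 and standardised difference 0.5 (assumed meaning of a medium effect): 50.15, rounded up to 51, or 102 in total. The present point does not contest it.
- True abstinence *p*: not given in the protocol. Assumed equal in both arms, 20%, with 10% and 30% as a range.
- Misclassification: not given. Let *f* be the share of true smokers recorded as abstinent in one arm only. Assumed 10%, 15% and 20%.

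Recorded abstinence in the affected arm = *p* + *f*(1 − *p*). In the other arm it stays at *p*.

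**3. Device misses smoking in the experimental arm, *p* = 0.20**

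- *f* = 0.10: 0.20 + 0.10 × 0.80 = 0.28, spurious difference +8 points
- *f* = 0.15: 0.20 + 0.15 × 0.80 = 0.32, spurious difference +12 points
- *f* = 0.20: 0.20 + 0.20 × 0.80 = 0.36, spurious difference +16 points

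For 0.32 versus 0.20, exact enumeration over two binomials with n = 51 gives these rejection probabilities at the 5% level:

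| Test | No misclassification | 0.32 vs 0.20 |
|---|---|---|
| Chi-square, uncorrected, two-sided | 0.050 | 0.286 |
| Fisher, two-sided | 0.029 | 0.219 |
| Uncorrected, one-sided for the experimental arm | 0.051 | 0.402 |

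Section 2.6 names chi-square or Fisher for the analysis and a one-tailed test for the sample size, so all three are shown.

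Across *p* = 10%, 20% and 30%, with a pooled z-test (normal approximation):

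- *f* = 0.10: +9, +8 and +7 points; one-sided rejection 0.36, 0.24 and 0.18
- *f* = 0.20: +18, +16 and +14 points; one-sided rejection 0.76, 0.56 and 0.43

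**4. The opposite direction**

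Suppose instead that the device records smoking correctly and only control participants under-report on paper. The same formula then applies to the control arm. At *p* = 0.20, *f* = 0.10 gives 20% versus 28% (−8 points, two-sided rejection 0.16) and *f* = 0.20 gives 20% versus 36% (−16 points, 0.44), both against the experimental arm.

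**5. One instrument in both arms**

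With the same *f* in each arm and equal true abstinence, recorded abstinence is equal, the expected difference is 0 and the normal-approximation error rate stays at 0.05.

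**The case against.** The strongest reply is that the outcome section settles the matter. It specifies self-report without distinguishing arms, Section 2.5.2 calls the diary paper-based, Section 2.4 likens the two arms' diaries, and the Discussion lists self-report as a limitation. The auto-compilation sentences sit in the description of the intervention and never say that device data feed CAR or PPA. They may be a stray remnant.

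Much of this stands. A reader might infer that ascertainment does differ by arm. The documents do not establish that: the difference arises only if the auto-compilation sentences are followed. But the objection does not remove the contradiction, because Section 2.5.1 routes self-report through the same diary that Section 2.3 says is auto-compiled.

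A reader might also infer that these devices cannot detect smoking. That goes too far. Section 2.3.2 mentions inertial sensors, introduces its device list as examples, and refers to manuals that are not shown. The text supports only that no smoking-event output is described.

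Nor do the documents support a bias in one direction only, since paper self-report can also be wrong. Finally, the misclassification rates above have no source in the protocol, so they show sensitivity and predict nothing.

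That an article condenses a fuller protocol is no answer here: the point is two incompatible statements in the text, and not an omission.

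**Conclusion.** The contradiction is explicit, in current text, and concerns the only named source of CAR and PPA. It should be resolved before enrolment, because arm-specific ascertainment could not be repaired by analysis afterwards. Certainty is high for the contradiction. Differential misclassification is a conditional consequence, of unknown direction and size. Under the assumed rates in the working (10% to 20% misclassified in one arm, true abstinence 10% to 30%), the spurious difference is 7 to 18 points either way. The sample size is unaffected.

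**What to change.** In Section 2.3, delete or correct the two sentences on detected smoking events and the automatically compiled diary. In Section 2.5.1, state that CAR and PPA in both arms come from the same self-completed paper diary, recorded and collected in the same way. Add that any device-derived smoking signal is exploratory, limited to the experimental arm, and neither feeds nor overwrites CAR or PPA.

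No additional abstinence question is needed to cure the contradiction. A second source would itself need a rule for disagreement with the diary.

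The cost is a change of wording. Section 2.7 reports that enrolment has not started, and no visit, measurement or participant is added.

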#### 2.3.1. Web-Based Telemedicine Platform

The BTS TELEREHAB platform (https://www.btsbioengineering.com/it/products/bts-telerehab/ accessed on 26 May 2026) is a web-based telemedicine system specifically designed to support remote multidisciplinary care, telemonitoring, and video consultations between healthcare professionals and participants. The platform is accessible through dedicated workstations and patient interfaces and integrates wearable medical devices for the automatic acquisition and transmission of physiological data, allowing real-time remote monitoring and review by the multidisciplinary clinical team. Data acquired from wearable devices and patient-reported outcomes will be automatically uploaded to the cloud-based platform.

To ensure patient privacy and data protection, all personal and clinical data collected through the telemedicine platform will be processed in accordance with the General Data Protection Regulation (GDPR; Regulation (EU) 2016/679). Participants will be identified using unique alphanumeric study codes, and only pseudonymized data will be used for study analyses.

Access to the platform will be restricted to authorized users according to their assigned roles, and the platform will implement appropriate technical and organizational measures to ensure the secure processing, storage, and transmission of health data in compliance with applicable data protection regulations.

#### 2.3.2. Wearable Remote-Monitoring Devices

The wearable remote-monitoring devices integrated with the BTS TELEREHAB platform are medical-grade, non-invasive tools, including wireless inertial sensors (e.g., G-SENSOR) and pulse oximeters (BTS Bioengineering S.p.A., Garbagnate Milanese, Italy). They collect the following physiological parameters: heart rate, blood pressure, respiratory rate, and peripheral oxygen saturation. Measurements will be collected twice daily for up to 12 months.

Data are acquired by the wearable devices and transmitted in real-time via a secure Bluetooth connection to the patient’s mini-PC Brain unit, which then forwards them to the cloud-based BTS TELEREHAB platform (https://www.btsbioengineering.com/it/products/bts-telerehab/ accessed on 26 May 2026) through an Internet connection (provided there is access to Wi-Fi or a portable hotspot). Data transmission uses encrypted protocols compliant with GDPR.

The system is designed for home and clinical use and has been validated in rehabilitation and telemedicine settings, as described in the BTS TELEREHAB (BTS Bioengineering S.p.A., Garbagnate Milanese, Italy) manuals.

Adherence to device use and data quality will be automatically monitored by the platform.

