#### 2.5.2. Secondary Outcomes

Secondary outcomes will include the longitudinal assessment of cardiopulmonary parameters, oral health conditions, smoking-related outcomes, health-related quality of life, oral health-related quality of life, and participants’ adherence, usability, acceptability, and patient and healthcare satisfaction with the rehabilitation program.

Cardiopulmonary parameters will include heart rate (beats per minute, bpm), blood pressure (mmHg), respiratory rate (breaths per minute), and oxygen saturation (SpO_2_, %). Heart rate, blood pressure, respiratory rate, and oxygen saturation will be measured twice daily throughout the 12-month study period. In the EG, these parameters will be automatically recorded twice daily through wearable remote-monitoring devices and transmitted to the integrated telemedicine platform. In the CG, the same parameters will be manually self-recorded twice daily using portable medical devices (sphygmomanometers and pulse oximeters) already available in participants’ possession. In addition, in-person clinical cardiology follow-up evaluations will be performed at baseline, 6 months, and 12 months by cardiology specialists for both EG and CG.Oral health outcomes will include probing depth (PD, mm) [29], full-mouth bleeding index (FMBI, percentage of bleeding sites) [30], and full-mouth plaque index (FMPI, percentage of plaque-positive sites) [31]. These clinical periodontal parameters will be assessed by calibrated dental specialists during standardized in-person periodontal examinations at baseline, 6 months, and 12 months. Periodontal examinations will be performed using a manual UNC-15 periodontal probe, and the periodontal parameters will be measured at six sites per tooth.

In addition, self-reported gingival bleeding during toothbrushing will be self-reported twice daily throughout the study period.

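### Control-arm respiratory rate has no stated counting method yet is set against an automatic experimental-arm stream, and the experimental-arm blood pressure instrument is not named

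*Protocol article*

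**What the plan says.** **Control arm.** Section 2.4 relies on portable devices that participants own, "such as sphygmomanometers and pulse oximeters, will be used to manually record heart rate, blood pressure, respiratory rate, and oxygen saturation twice a day". Section 2.5.2, which defines the outcome, says the same four parameters are "manually self-recorded twice daily using portable medical devices (sphygmomanometers and pulse oximeters) already available in participants’ possession". Neither section says how breaths are to be counted.

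**Experimental arm.** Section 2.5.2 says that "these parameters will be automatically recorded twice daily through wearable remote-monitoring devices and transmitted to the integrated telemedicine platform", and Section 2.3 says the same of the wearables. Section 2.3.2 describes the device set as "including wireless inertial sensors (e.g., G-SENSOR) and pulse oximeters" and continues: "They collect the following physiological parameters: heart rate, blood pressure, respiratory rate, and peripheral oxygen saturation".

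**Eligibility.** Section 2.2 excludes "Participants without access to home medical devices for monitoring cardiopulmonary parameters (blood pressure monitor and pulse oximeter), required to perform the scheduled home assessments". It does not limit this to one arm. Section 2.4 and the Discussion tie the requirement to the control group.

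**Use of the data.** Section 2.5.2 lists the cardiopulmonary parameters as secondary outcomes. Table 1 marks respiratory rate and blood pressure in every column from baseline to close-out. Section 2.6 plans between-group tests of continuous variables, and mixed-effects models over baseline, 6 and 12 months. Section 2.5.2 also schedules in-person cardiology evaluations in both arms at those three times.

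**The concern.** An outcome can be compared between arms only if each arm has a defined way of producing it. For control-arm respiratory rate, the two named devices are a blood pressure instrument and an oximeter. The protocol describes neither as giving a breathing rate, and it supplies no counting instruction. Participants who follow the text would leave the field blank or count their own breaths in whatever way occurs to them. The experimental arm's values arrive by an automatic route. A difference between arms could then reflect how the number was obtained, or who managed to supply one, rather than any effect of the programme.

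The second part concerns blood pressure in the experimental arm. Automatic capture and remote review are part of the intervention being tested (Sections 2.3 and 2.3.1). If the instrument is not identified, neither the outcome nor that part of the intervention can be reproduced from the text.

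**Working it through.** The protocol gives no figure to reproduce on this point. The check is to match each parameter with the devices named for each arm in Sections 2.2, 2.3.2, 2.4 and 2.5.2.

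| Parameter | Experimental arm | Control arm |
|---|---|---|
| Heart rate | Named source (pulse oximeter) | Named source (oximeter or sphygmomanometer) |
| Oxygen saturation | Named source (pulse oximeter) | Named source (pulse oximeter) |
| Blood pressure | Automatic; no blood pressure device among those named | Named source (sphygmomanometer) |
| Respiratory rate | Automatic; an inertial sensor is a plausible source, but the text does not say so | No named device or counting method |

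**Count.** Two of four parameters have a gap: blood pressure in the experimental arm and respiratory rate in the control arm.

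**Is the control list open or closed?** Section 2.4 introduces the devices as examples, so another device could be meant. Section 2.5.2 gives the same two device types in brackets without that qualifier. The outcome definition therefore reads as a closed list.

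**Does manual recording settle it?** It could mean counting breaths. But Section 2.5.2 says the values are recorded using the two devices, and self-counting is not mentioned. If self-counting is intended, the counting period and conditions are left to each participant.

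**Is the experimental list open or closed?** Open: the two device types are introduced as examples. The set as a whole is said to collect blood pressure, so one member may simply be unnamed. Against this, the protocol lists a blood pressure monitor beside the pulse oximeter wherever it describes home equipment (Sections 2.2, 2.4 and 2.5.2), so it treats the two as separate items. The validation statement in Section 2.3.2 is general and does not mention blood pressure.

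**Could the home monitor in Section 2.2 supply experimental-arm blood pressure?** The criterion is worded for all participants, so experimental participants may own one. But Section 2.5.2 assigns that arm's readings to the wearables, and nothing describes a participant-owned monitor feeding the platform.

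**Would a common measurement fit the planned analysis?** Yes. The mixed-effects models in Section 2.6 use baseline, 6 and 12 months, the times of the in-person visits. Section 2.1 places the baseline assessment before the allocation envelope is opened, so a staff count there would precede allocation.

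**The case against.** The strongest reply is that this is missing detail. A journal article need not carry a device inventory or a counting instruction; the full protocol and the cited device manuals may do so. For blood pressure in the experimental arm much of this stands, because the list is open and the text expressly says the set collects blood pressure. For respiratory rate in the control arm it stands less well: the difficulty there is what the outcome definition states, namely a closed pair of devices offered as the means of recording a breathing rate.

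A second reply is that a self-counted rate is still a source and can be reported. That is fair. It does not make the rate comparable with an automatic one.

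A reader might also infer more than the documents support:

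- **That the named experimental devices cannot measure blood pressure.** Showing this would need device specifications, which are not in the document.
- **That these are safety parameters, or that clinicians would wrongly believe they were watching blood pressure.** The protocol calls them secondary outcomes. Section 2.3.2 says the platform monitors device use and data quality, so an absent stream should be visible.
- **That a very large number of readings is lost.** The schedule allows at most 2 × 365 = 730 readings per participant per parameter, or 730 × 51 = 37,230 per arm. That ceiling assumes full adherence for 12 months, although Section 2.3 makes device use voluntary in the experimental arm. It measures neither loss nor bias.

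**Conclusion.** The point holds for respiratory rate and, more weakly, for blood pressure. As written, the between-arm respiratory-rate outcome would compare an automatic stream with blank or self-counted control values. Experimental-arm blood pressure is attributed to a set with no named blood pressure device; this is a gap in identification, not proof of incapability.

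The extent is two of four cardiopulmonary parameters, one per arm, both secondary outcomes. The size and direction of any resulting bias cannot be derived from the document. The abstinence outcome and the sample size of 102 do not depend on these measurements.

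The conclusion assumes that participants' own sphygmomanometers and oximeters do not generally display a respiratory rate. If some do, control values would come from a mixture of sources, which the protocol does not define either.

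**What to change.** **Respiratory rate.** In Section 2.5.2, define the between-arm outcome as a rate counted by staff, by the same stated method in both arms, at the baseline, 6- and 12-month in-person visits. Treat home values as descriptive, and state in Sections 2.4 and 2.5.2 how control participants obtain them.

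**Blood pressure.** In Section 2.3.2, name the connected instrument used in the experimental arm. If there is none, state that readings are entered by hand, and remove blood pressure from the automatic stream in Sections 2.3, 2.3.2 and 2.5.2.

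**Eligibility.** Reconcile the home-device criterion in Section 2.2 with Section 2.4 and the Discussion, so that it is clear whether it applies to everyone or to one arm, and how it relates to experimental-arm recording.

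**Cost.** Protocol wording and one short count at visits already scheduled. Section 2.7 says enrolment has not started, so no collected data are affected. The downside is fewer time points: the respiratory-rate comparison would rest on three visits rather than a twice-daily series. Those three visits are the times the planned mixed-effects models use. A staff count would not be blinded in this open trial, but both arms would be measured in the same way.
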